### Recruitment {15}

We were able to recruit 136 prisoners in only 1 day at the SCCCfor our feasibility study. The success of this recruitment was primarily due to what the trial was able to offer: a perception of increased muscle strength [52] and receiving compensation for inconvenience ($30 at baseline and $50 post-trial). Taking into account the inclusion criteria of this multi-centre trial, of those 136 prisoners, 34 would be excluded due to high omega-3 index (data from our feasibility study). Given that recruitment will occur at multiple centres with one or two cohorts per site as necessary, we anticipate comfortably meeting our targets of 600 prisoners and 360 completions.

## Assignment of interventions: allocation

### Sequence generation {16a}

Participants will be block randomised (according to their IBOS, age and baseline omega-3 index) within each treatment centre to one of the 2 study arms. The randomisation will be performed by Chief Investigator MB (biostatistician) using the RALLOC command in STATA V12 or higher (College Station, TX).

### Concealment mechanism {16b}

Allocation will occur following the assessment of participant eligibility. Participants will be allocated to group A or group B by block randomisation. A person independent of the study will allocate the control and experimental cohorts to group A or B and will hold the allocation key in a sealed envelope. Supplement jars will not be labelled with group identification, only participant’s identification such that each study participant has their own allocated supplements without the labels ‘A’ or ‘B’ on them. Participants and the Project Officer will be blinded to the intervention group allocation throughout the study.

### Implementation {16c}

The generation of allocation sequence will be performed by Chief Investigator MB (biostatistician) using the RALLOC command in STATA V12 or higher (College Station, TX). One designated Project Officer on secondment to the research trial at each of the sites will enrol the potential participants at their respective sites.

## Assignment of interventions: blinding

### Who will be blinded {17a}

Project Officers administering the supplements, participants receiving the supplements and the people assessing the outcomes and analysing the data will be blinded to interventions. The randomisation list will be managed through an independent third party who will keep treatment allocation totally blinded.

### Procedure for unblinding if needed {17b}

It is anticipated that unblinding the trial will not be necessary. Revealing a participants’ allocation intervention during the trial will not be necessary.

## Data collection and management

### Plans for assessment and collection of outcomes {18a}

Correctional Officers on secondment to the research project as Project Officers will attend a 3-day training workshop at the University of Wollongong. They will be educated on research rationale and the anticipated outcomes. They will be trained in (1) how to translate the written case notes into a numerical IBOS score; (2) how to approach potential study volunteers in a culturally sensitive way; (3) the process for baseline and post-intervention assessments (including the procedures for blood collection, and how to conduct the questionnaires and use the dynamometer to measure muscle strength); (4) how to deliver the capsules and check for compliance; and (5) how to enter the data in the database.

A manual outlining the standard procedures for screening, recruitment, data collection and completing the study will be given to Project Officers.

The IBOS is a validated tool that can be used across jurisdictions and has high inter-rater reliability. The questionnaires are all validated and are used frequently in this area of research. The blood omega-3 assessments are routinely conducted in CIA BJM’s laboratory at the University of Wollongong.

### Plans to promote participant retention and complete follow-up {18b}

Project Officers will routinely discuss participant experience of the trial as the capsules are delivered. In doing so, participant indication of a desire to discontinue trial engagement will be discussed and where individual problems associated with participation are identified, the Project Officer will assist the participant to problem solve a solution to enable ongoing participation.

### Data management {19}

The post-doctoral person at UOW, CHC, will be responsible for data collation and ensuring data quality control checks under the supervision of CIA BJM and CIB MKB.

The on-site data will be collected using excel templates: one identifiable and one de-identifiable. The identifiable dataset will be stored on a secure server at Correctional Centre Head Office and will ultimately be used to assess recidivism. The study participants will be given a unique identifier that incorporates their Correctional Centre and a three-digit number and all intervention data will be captured in this de-identified dataset. This de-identified data will ultimately be imported into RedCap (Research Electronic Data Capture [65, 66]) and hosted at the University of Wollongong local servers and external hard drive. The de-identified dataset will be protected by a password or RedCap’s data access groups. Access to the dataset will be on a needs basis and certainly provided to our biostatistician who will be primarily responsible for the data analysis. Data quality control checks will be carried out during recruitment and post-interventions, and prior to analysis. Data quality checks will include range checks, duplicate checks, missing data checks and checks for data entry errors.

### Confidentiality {27}

The Correctional Officers seconded to the research study as Project Officers will enter data into two datasets: (1) a re-identifiable dataset that contains personal information and the study participants’ unique identifier code and (2) a de-identified dataset, where all the collected data from the research trial is entered. The re-identifiable dataset will be held in Correctional Services Head Office and will be used for assessing rates of recidivism. The de-identified dataset will be held with the researchers. The data files will be kept in secure locations at the UOW with appropriate back-up.

### Plans for collection, laboratory evaluation and storage of biological specimens for genetic or molecular analysis in this trial/future use {33}

Upon written consent, the potential study participant’s medical records will be checked to determine if they are taking blood thinning medications or are physically unfit to take part in the research trial. Chief Investigator DG who has medical qualifications will assess the potential study participant’s medical eligibility. A baseline blood sample will be taken from the eligible study participants by qualified staff from Pathology centres. The blood samples will be analysed for omega-3 index in Chief Investigator BJM’s laboratory at the University of Wollongong. Those prisoners with an omega-3 index of less than 6% will be eligible to commence the intervention trial, on the provision that they forgo purchase of additional fish (tuna, salmon) and n-3 LCPUFA supplements from their casual ‘buy up’ for the duration of the trial. They will be offered compensation for inconvenience: $30 after the baseline assessments and $50 after the completion of all the post-intervention assessments.

Blood samples will be stored in a BioBank from those prisoners that consent to their blood samples being stored. Future research may be conducted using these stored blood samples after obtaining the necessary ethics approval.

## Statistical methods

### Statistical methods for primary and secondary outcomes {20a}

In the simplest case, this study is designed to determine the difference between groups as proportion of responders to the treatment allocation. This analysis will be performed using a generalised linear mixed model adjusted for clustering by prison. IBOS scores will also be analysed using a form of generalised linear mixed model or generalised additive mixed models depending on the final distribution of the IBOS scores. These models also allow for the correlated nature of repeated measures over time and the correlation between prisoners from the same institution. Secondary measures will be analysed using linear mixed, or generalised linear mixed models again depending on the distributional form of the variable. These analyses will be conducted using STATA or R.

The data will also be analysed according to the change in the omega-3 index [24] as recommended by ISSFAL [24].

Our policy implementation is based on the primary outcome measure, the IBOS. The secondary outcome measures are hypothesis generating.

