### Sample size {14}

Our study is a randomised controlled trial powered to show a difference between treatment and placebo control of 25% in the proportion of participants experiencing a reduction in aggressive behaviour as measured by a change in the IBOS. Given the nature of the prison populations, it is likely that there will be an effect of prison in the analysis, and therefore, a design effect accounting for the intra-cluster correlation is incorporated in the sample size estimation with a conservatively estimated ICC of 0.03. Based on our pilot data, we anticipate that attrition will likely be high (~ 40%) with the sample size for recruitment appropriately inflated to account for this. Overall, a total sample size of 600 with 360 completing the study enables a difference of 25% to be detected with 80% power and an alpha level of 0.05.

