### Methods for additional analyses (e.g. subgroup analyses) {20b}

A priori, a subgroup per protocol analysis is planned for those participants deemed to be compliant with treatment. Subgroup analysis that will be considered include 80% compliance to capsule regime, age as a covariate, per change in omega-3 as recommended by the ISSFAL [24] and the Aggression Questionnaire—high vs low dispositional aggression.

The covariates that might be adjusted for include baseline DASS scores and SF-36 scores. It is acknowledged that reactive aggression is influenced by depression, anxiety and stress and this will be identified through the DASS. The dispositional ‘satisfaction’ will be assessed via the SF-36. With respect to ADHD, we hypothesise a mediating role of ADHD in aggressive behaviour.

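### The responder model names prison only, although randomisation is also blocked on IBOS, age and omega-3 index; the test stays valid, but adjusting for these factors is a free improvement

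*Protocol article*

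**What the plan says.** All references are to the protocol article; no separate analysis plan is shown.

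- **Sequence generation {16a}:** "Participants will be block randomised (according to their IBOS, age and baseline omega-3 index) within each treatment centre". The cut-points for the three factors are not given.
- **Statistical methods {20a}:** the responder analysis estimates "the difference between groups as proportion of responders to the treatment allocation". On the model: "This analysis will be performed using a generalised linear mixed model adjusted for clustering by prison". No other adjustment is named.
- **Statistical methods {20a}, IBOS scores:** a further mixed model is planned. "These models also allow for the correlated nature of repeated measures over time", but whether baseline IBOS is a covariate or one of the time points is not said.
- **Additional analyses {20b}:** "The covariates that might be adjusted for include baseline DASS scores and SF-36 scores". Age occurs only as "age as a covariate", inside a list of subgroup analyses to be considered.
- **Sample size {14}:** response is a "reduction in aggressive behaviour as measured by a change in the IBOS".

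Baseline IBOS and baseline omega-3 index are nowhere named as adjustment covariates. In the analysis sections the omega-3 index appears only as change from baseline.

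**The concern.** Blocking on a prognostic factor makes the arms more alike than simple randomisation would. An analysis that ignores the factor does not credit that balance, so its standard error is too large for the design used. In a logistic-type model, omitting a prognostic factor also pulls the treatment odds ratio towards 1.

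The article gives some reason to expect prognostic value:

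- **Baseline IBOS** is one component of the change that defines response. Eligibility {10} admits only men with a score above 0, on a scale that runs from −1 to 5. Selection on a raised score invites regression to the mean, and the room to fall depends on the starting score.
- **Omega-3 index:** the Background reports negative baseline correlations with aggression, and the Discussion reports that men below 6% were 4.3 times more likely to have an IBOS above 2. These are cross-sectional findings, and entry is restricted to men below 6%, so the association with response inside the trial may be weaker.
- **Age:** the article gives no evidence either way.

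There is a second, smaller issue. Section {20a} bases policy implementation on the IBOS, so it should be clear in advance which adjusted model supports the main claim. A tentative covariate list that omits the blocking factors does not make it clear.

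**Working it through.** **1. The plan's own figure.** Inputs from Sample size {14}: 25% difference (read as absolute), 80% power, alpha 0.05 (two-sided assumed), ICC 0.03, 40% attrition, 600 recruited and 360 completing. From Study setting: at least 6 centres (6 assumed). The control response rate is not stated; 25% against 50% is assumed.

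- Completers per prison: 360/6 = 60. Clustering factor: 1 + (60 − 1) × 0.03 = 2.77.
- Two-proportion formula with continuity correction: 66 per arm (58 without).
- Completers: 2 × 66 × 2.77 = 366. Recruited: 365.6/0.6 = 609.
- Stated: 360 and 600 (360/0.6 = 600 exactly).

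The figure is reproduced to within 2% under these assumptions. It takes no credit for covariates, so adding them does not change it.

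**2. Effect of leaving out the blocking factors.** The check simulated 6 prisons with 60 completers each, 1:1 allocation in blocks of 4 within prison and three two-level factors, with 1,500 runs per scenario. A logistic model with prison alone was compared with prison plus the three factors. Prison was a fixed effect, standing in for the mixed model. The odds ratios linking the factors to response are assumed, because the article gives none.

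Type I error:

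| Assumed prognostic strength | Prison only | Prison + factors |
|---|---|---|
| None | 0.055 | 0.055 |
| All three OR 1.5 | 0.056 | 0.058 |
| IBOS OR 3, others 1.5 | 0.041 | 0.049 |
| IBOS OR 6, others 2 | 0.029 | 0.049 |

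The Monte Carlo standard error at 0.05 is √(0.05 × 0.95/1500) = 0.0056. Only 0.029 is clearly away from nominal, and it is on the conservative side.

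Power (%):

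| Assumed prognostic strength | Log-OR 0.6: prison only | Log-OR 0.6: + factors | Gain (points) | Log-OR 1.02: prison only | Log-OR 1.02: + factors | Gain (points) |
|---|---|---|---|---|---|---|
| None | 81.6 | 81.7 | 0.1 | 99.7 | 99.7 | 0.0 |
| All three OR 1.5 | 77.5 | 79.3 | 1.8 | 99.2 | 99.3 | 0.1 |
| IBOS OR 3, others 1.5 | 74.4 | 76.5 | 2.1 | 99.7 | 99.7 | 0.1 |
| IBOS OR 6, others 2 | 64.5 | 73.0 | 8.5 | 98.2 | 98.9 | 0.7 |

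Gains are taken before rounding. With rates placed evenly around 50% and no prognostic factors, log-OR 1.02 is 1/(1 + e^−0.51) − 1/(1 + e^0.51) = 0.625 − 0.375 = 25 points. Log-OR 0.6 is 0.574 − 0.426, about 15 points.

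**3. Why these powers exceed the planned 80%.** The simulation compares arms within prisons, so differences between prisons cancel. The plan divides its information by 2.77. A plain two-proportion calculation with 180 per arm and no clustering factor gives 99.8% for 37.5% against 62.5%, in line with the first row.

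**The case against.** The best defence is that the article does not exclude covariates. The sentence on the responder model is introduced as the simplest case, the list in {20b} is open-ended, and a condensed article may leave the full covariate list to an analysis plan that is not shown. DASS and SF-36 appear under additional analyses, so they are not clearly offered for the primary model, and age adjustment is at least contemplated. The IBOS score model may already use baseline IBOS as a time point.

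Much of this stands. It rules out saying that the primary model is fixed to exclude the blocking factors. It does not remove the mismatch: the article takes up both the model and the covariates, and what it names differs from what it randomises on.

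A reader might infer more than the text supports:

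- **That the blocking is wasted or the test invalid.** It still balances the arms, and type I error stays at or below about 5% within simulation error.
- **That baseline IBOS is the strongest predictor.** The article gives no association between baseline IBOS and response; the argument from regression to the mean is plausible but unquantified.
- **That adjustment is worth many extra participants.** The linear-model factor 1 − ρ² would give 360/0.64 = 563 at an assumed correlation of 0.6. That applies to a continuous score compared without baseline adjustment, not to the binary responder model.
- **That a random prison intercept is inadequate.** The article does not specify one, and fixed or random prison effects are a matter of preference here.

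**Conclusion.** The point holds as a modest, cost-free improvement. Followed as written, the responder analysis is valid but no more efficient, and possibly less efficient, than one that uses the factors already randomised on. Adjusted power was at least equal in every scenario. For an effect smaller than planned (log-OR 0.6) the loss from omission was 0.1 to 2.1 points in three scenarios and 8.5 points in the strongest. Near the planned 25 points it was at most 0.7 points.

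These sizes rest on assumed odds ratios, 6 equal prisons, two-level factors and fixed prison effects. If the factors are not prognostic, nothing is lost by omitting them and nothing is lost by including them. The result does not show that the trial is underpowered.

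**What to change.** Before unblinding, state the following in the protocol or analysis plan:

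1. The primary responder model contains arm, baseline IBOS, age, baseline omega-3 index and prison. If any blocking factor is left out, give the reason.
2. The treatment effect is reported as a standardised risk difference: predict each participant's response probability under both arms, average over participants and subtract, with a confidence interval. This matches the difference in proportions in {14} and {20a}; an adjusted odds ratio alone would not.
3. Baseline IBOS enters the IBOS score model, and how it enters is stated.
4. Adjustment for baseline DASS and SF-36 is a prespecified sensitivity analysis. Age is listed as a model covariate, not under subgroup analyses.

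The cost is a few sentences of analysis wording. All three factors must be known before a man can be randomised, so no new data are needed and the sample size stays at 600.

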### Interim analyses {21b}

Not applicable, as there is no need for interim analyses.

### Methods for additional analyses (e.g. subgroup analyses) {20b}

A priori, a subgroup per protocol analysis is planned for those participants deemed to be compliant with treatment. Subgroup analysis that will be considered include 80% compliance to capsule regime, age as a covariate, per change in omega-3 as recommended by the ISSFAL [24] and the Aggression Questionnaire—high vs low dispositional aggression.

The covariates that might be adjusted for include baseline DASS scores and SF-36 scores. It is acknowledged that reactive aggression is influenced by depression, anxiety and stress and this will be identified through the DASS. The dispositional ‘satisfaction’ will be assessed via the SF-36. With respect to ADHD, we hypothesise a mediating role of ADHD in aggressive behaviour.

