#### Addressing the n-3 LCPUFA controversy

Randomised controlled trials and meta-analysis of trials up to 2002 demonstrated that supplementation with n-3 LCPUFA resulted in up to 45% reduction in overall mortality from cardiac death [5, 16]. However, reviews and meta-analyses of more recent trials reported a lack of efficacy, questioning whether increased n-3 LCPUFA levels improve health outcomes [17, 18]. Nevertheless, critical analyses of these recent trials have suggested that their observed lack of efficacy may have been due to methodological problems arising across populations studied [19]. Following the earlier successful trials, the American Heart Association issued guidelines for people with heart disease, suggesting consumption of at least 2 fish meals per week [20] in addition to fish oil supplements [21]. Between 2000 and 2010, the importation of fish oils into the USA escalated more than 10-fold from 2000 to 22,000 metric tonnes [22]. However, trials conducted after 2002 failed to screen people for high fish and/or fish oil supplement intake resulting in great variability of n-3 LCPUFA status across trial conditions [19]. Where screening did occur, the upper 50% of the control subjects and the lower 50% of the fish oil intervention subjects overlapped [23], suggesting that the 2 groups were not separated enough in use of fish oils to demonstrate an effect in the test arm (n-3 LCPUFA). Thus, robust trials of using fish oil to address omega-3 deficiency need to attenuate possible ceiling effects created by high baseline levels, by taking blood samples to determine compliance and correlations between increased omega-3 index and response. This is supported by the International Society for the Study of Fatty Acids and Lipids (ISSFAL) recent position statement, which highlights the importance of measuring blood n-3 LCPUFA levels in research [24].

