## Discussion

At least 45% of prisoners in Australia are incarcerated for violent offences [67]. Approximately 46% of prisoners have experienced a mental health disorder [68]. The rate of prisoner on prisoner assault reported in NSW and QLD prisons is 34% [69].

Prisoners cost the nation $2.6 billion in 2013–2014 after expenses, with the average daily cost per prisoner exceeding the average Australian’s daily income [70]. Should the intervention reduce aggressive behaviour by 25%, the estimated impact upon institutional violence would be an 8.5% reduction based on extant assault prevalence rates (34%). Some estimations of cost savings across prison populations nationally would suggest up to $236 million/year (at a conservative $8500 per aggressive prison patient prevented). This intervention also has potential to enhance overall prisoner health outcomes and if omega-3 use is maintained post-incarceration to reduce violent recidivism.

Our feasibility study showed that prisoners are 4.3 times more likely to have an IBOS of > 2, if they are below the cutoff of 6% omega-3 index [38] but this does not show causality. This multi-centre trial is adequately powered to demonstrate the effect of n-3 LCPUFA on aggressive behaviour in adult male prisoners. The strengths of this study include the IBOS, measuring n-3 LCPUFA levels in the blood and, after demonstrating efficacy, rolling out into policy and practice and the health economics. The IBOS eliminates cross- and intra-jurisdictional variations in reprimands, robustly accounting for prisoner aggressive behaviours. The blood n-3 LCPUFA assessments will verify that the reduction in aggressive behaviour is related to an increase in n-3 LCPUFA. Once we demonstrate efficacy, we will translate into policy and practice across all jurisdictions in Australia. Given the high costs associated with prisoner aggressive behaviour, substantial cost savings are expected.

Our research team has the track record to navigate studies through the ethics approval process, as evidenced by the feasibility studies and publication outcomes [7, 53]. This research will be carried out in accordance with the Declaration of Helsinki [44] and the Australian National Statement on Ethical Conduct in Research Involving Humans [71]. This research will follow the CONSORT guidelines and is registered with the Australian New Zealand Clinical Trials Registry.

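### The only omega-3 subgroup variable named is post-randomisation change in the index; the baseline index, which is measured and blocked on, is not examined as an effect modifier

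*Protocol article*

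**What the plan says.** The protocol article's section Methods for additional analyses {20b} gives the subgroup analyses under consideration: 80% capsule compliance, age, omega-3 "per change in omega-3 as recommended by the ISSFAL", and high against low Aggression Questionnaire disposition. The covariates it says might be adjusted for are baseline DASS and SF-36 scores. The main section Statistical methods {20a} also plans an analysis by change in the omega-3 index. Neither section uses the baseline index as a subgroup, an interaction or a covariate.

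Elsewhere the baseline index is central:

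- It is measured by a blood sample before entry, and only men below 6% may start (Eligibility criteria {10}; Plans for collection {33}).
- Men are "block randomised (according to their IBOS, age and baseline omega-3 index) within each treatment centre" (Sequence generation {16a}).
- The background argues that trials "need to attenuate possible ceiling effects created by high baseline levels".
- The Discussion reports that in the feasibility study "prisoners are 4.3 times more likely to have an IBOS of > 2, if they are below the cutoff of 6% omega-3 index", and adds that this is not evidence of causality.

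**The concern.** A subgroup analysis asks whether the randomised effect differs between kinds of participant. The variable that defines the subgroups must therefore be fixed before treatment can act on it. Change in the index is not. It is what the active capsule is meant to produce, and sections {11a} and {11c} use it as a measure of adherence. Men with a large rise are mostly men who were given the active capsules and took them. A comparison by change therefore mixes treatment, adherence and whatever else distinguishes adherent men, with few placebo men in the high-change stratum. It also needs a second blood sample, so men who leave without giving one drop out of it.

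The baseline index has none of these faults. It is known for every entrant, precedes randomisation and is already balanced by the blocking. The article names the omega-3 variable that can mislead and leaves out the one that randomisation protects. At stake is whether the trial can say, on a randomised basis, if benefit varies with entry status within the enrolled range.

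**Working it through.** **1. The plan's own sample size.** Inputs from Sample size {14}: a "difference between treatment and placebo control of 25% in the proportion of participants experiencing a reduction in aggressive behaviour", read as 25 percentage points; 80% power; alpha 0.05 (two-sided assumed); "with a conservatively estimated ICC of 0.03"; about 40% attrition; 600 recruited and 360 completing. At least 6 centres gives 360/6 = 60 completers per centre. The control response rate is not stated, so it is assumed.

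- Attrition: 360/(1 − 0.40) = 600. This agrees.
- Design effect: 1 + (60 − 1) × 0.03 = 2.77.
- 25% against 50%, with continuity correction: 66 per arm, and 2 × 66 × 2.77 = 366, close to 360.
- Without the correction, control rates of 20% to 50% need 300 to 344 completers, so 360 gives 82% to 87% power.

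The main-effect size can be reproduced and is not in dispute. The article gives no figure for any subgroup or interaction.

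**2. What a split on change can show.** An illustrative simulation used 2,000 trials of 180 per arm and no treatment effect. These assumptions are not in the article:

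- A behavioural trait related to adherence raises the chance of response.
- In the active arm only, the same trait drives the rise in the index.
- Random noise is added to the change.

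Results:

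- Split at the active-arm median of change, active men above it responded 9.5 points more often than active men below it, although the capsule did nothing.
- No placebo men fell in the high-change stratum.
- Split at the median baseline index, the mean difference in treatment effect was 0.003. The between-trial SD was 0.103, so the Monte Carlo error is 0.103/√2000 = 0.002, and the result is compatible with zero.

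The size of the spurious gradient depends on these assumptions. That such a gradient can arise does not.

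**3. What a baseline-index interaction could detect.** With 1:1 allocation balanced on the index, each arm's slope has variance σ²/((N/2)·SDx²). The difference of two slopes therefore has SE = 2σ/(√N·SDx). The multiplier for 80% power is 1.96 + 0.84 = 2.80.

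- N = 360: SE = 2/√360 = 0.105; detectable 2.80 × 0.105 = 0.295 outcome SD per SD of index.
- N = 600, if all have outcomes: 2.80 × 2/√600 = 0.229.
- Responder endpoint, SE = 2/√(N·p(1 − p)), with assumed overall response p:
  - p = 0.45: 2.80 × 2/√(360 × 0.2475) = 0.593; ratio of odds ratios 1.81 per SD.
  - p = 0.65: 2.80 × 2/√(360 × 0.2275) = 0.619; ratio 1.86 per SD.

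**4. Cruder version, median split.** There are 90 completers per arm in each half, with assumed control response 25% to 50%. At 25% control and a 25-point effect in both halves, SE = √(2 × (0.1875 + 0.25)/90) = 0.099, so the detectable difference between halves is 2.80 × 0.099 = 0.276.

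| | No design effect | Design effect 2.77 |
|---|---|---|
| Difference between halves detectable with 80% power | 26 to 29 points | 44 to 48 points |
| Power for effects of 35 against 15 points | 51% to 54% | 22% to 23% |

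Men are randomised individually within centres, so this contrast is largely within-centre. The 2.77 column is a pessimistic bound.

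**The case against.** The strongest reply is that this is a condensed article and that the choice of exploratory interactions belongs in an analysis plan. The list is also introduced as analyses to be considered, so it is not closed. Both points are fair. Had the article been silent on omega-3 modifiers there would be nothing to raise. But it is not silent: it names one, and the one it names is post-randomisation. An open list permits the valid analysis without committing to it.

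It can also be said that the change analysis matches the article's rationale, which asks for correlations between a rising index and response and cites a recommendation for measuring blood levels. That supports keeping it as an exposure-response analysis, not as a subgroup. No aim or hypothesis claims that benefit varies with the baseline index, and power for the interaction is low. These points stand and are why it should be exploratory.

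Two stronger readings are tempting and are not supported:

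- A reader might infer that the deficiency rationale goes untested. It does not. The below-6% entry rule handles the ceiling concern by design, and the randomised main effect tests supplementation in low-index men.
- A reader might infer that an index-based policy threshold hangs on this analysis. The article proposes none. Its policy framework speaks of minimum intake and a supplementation schedule, section {20a} bases policy on the IBOS, and the 6% association is expressly non-causal.

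**Conclusion.** The point holds in a limited form. The only omega-3 subgroup variable named is a consequence of allocation and adherence, so it cannot validly show for whom supplementation works. No analysis named in the article examines whether the effect varies with the baseline index below 6%. The primary comparison and the sample size are unaffected.

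The replacement analysis would detect only large gradients: about 0.30 outcome SD per SD of index with 360 completers, or a ratio of odds ratios of about 1.8 to 1.9 per SD. In the median-split version without a design effect, the difference between halves would have to exceed the 25 points planned for the whole trial. These figures assume two-sided 5% testing, balance on the index, no clustering inflation for the within-centre contrast and, for the binary endpoint, the assumed response rates. How completely strata of change separate the arms depends on adherence, but change remains a post-randomisation variable even where the arms overlap.

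Entry is truncated at 6%; the article notes that 34 of 136 pilot recruits (25%) would be excluded for a high index. The interaction therefore describes only the range below 6%. It cannot test a ceiling at high levels or validate the cutoff, and a null result would say little.

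**What to change.** In section {20b}:

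1. Name treatment × baseline omega-3 index as the omega-3 effect-modifier analysis, with the index continuous and as measured before randomisation. Fit it in the primary model with the baseline index as a main effect, which is also apt because it is a blocking factor. Report the interaction estimate with its 95% CI and label it exploratory.
2. Remove change in the index from the subgroup list. Keep it, here and in section {20a}, as a non-randomised exposure-response analysis described as such.
3. State that power is limited (about 0.30 outcome SD per SD of index with 360 completers) and that the result applies only below 6% and does not validate that cutoff.

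The cost is one model term and a few sentences, with no new data or participants. The downside is one more exploratory test.
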